**Figure 2 F2:**
[figure not shown]
**Design of study**.

The end point of the training phase of the study for Group A will be 4 months and for Group B will be 2 months. The end point of the follow-up phases of the study will be 6 months and 12 months after admission to the study for all groups.

### Participants

People with stroke will be screened and invited to participate if they:

1. are within 5 years of their first stroke, are adults capable of providing consent, defined as having a Mini Mental State Exam score of > 23 have been discharged from formal rehabilitation and are community-dwelling;

2. walk slowly, defined as 'being able to walk 10 m across flat ground in bare feet without any aids with a speed of less than 1 m/s.

Participants suitable for inclusion in the study need permission granted by their medical practitioner before admission to the study. They will be excluded if they:

1. have an unstable cardiac status which would preclude participation in a treadmill training program (i.e., permission not granted by their medical practitioner), or

2. have severe cognitive and/or language (aphasia) deficits which would preclude them from participation in the training sessions (i.e., unable to follow 2-step commands).

Interpreters will be used for those participants for whom English is difficult.

### Randomisation

Randomisation will be computer-generated, independent and concealed. Participants will be recruited in cohorts of 15. Each cohort will be ranked in descending order according to comfortable walking speed over 10 m and then organized into matched triplets. The participants in each triplet will then be assigned to Group A or B or C by random allocation generated by computer in order to provide secure randomisation, concealed from the recruiter. In this way, participants will be stratified according to initial level of walking disability since this has been found to affect outcome [18].

### Intervention

Training for both intervention groups will be based on a previously-successful treadmill walking program [17]. It will be carried out 3 times a week and the sessions will comprise 30 min of walking. Participants will receive individual training from a physiotherapist; however, there will be opportunity for social interaction since several participants will be trained concurrently. The program will be carried out in a community setting and transport will be provided if necessary. Guidelines will outline the progression of training. Information describing the specific features of the training session (such as treadmill speed, distance walked, assistance required, etc) will be recorded to monitor adherence to the guidelines and to be able to describe the intervention accurately.

Treadmill walking will be structured to increase stride length, speed, workload, and automaticity. To increase stride length, the treadmill will be run at a comfortable speed and participants will be instructed to "walk as slowly as possible". In addition, marching type steps will be included to encourage hip and knee flexion during swing phase to improve toe clearance. A metronome may also be used to decrease cadence and to encourage larger steps. When a normal step length is observed, the speed of the treadmill will be increased (until step length is compromised). Workload will then be addressed by increasing the incline of the treadmill. Finally, automaticity will promoted by presenting the participants with a concurrent cognitive task while maintaining speed and normal step length. The cognitive task may include the participant holding a conversation with the physiotherapist or may be a more structured task such as matching the word "red" with the response "yes" or the word "blue" with the response "no". During treadmill walking, attention will also be focused on alignment to help participants keep their trunk vertical.

The gains achieved during treadmill walking will be reinforced with some overground walking each session, starting with 20% overground walking and working up to a maximum of 50%. Overground walking is defined as whole task practice involving propulsion forwards, backwards, sideways or up and down stairs. To reinforce the increased stride length achieved during treadmill walking, visual cues will be supplied in the form of non-slip footprints which will be laid at intervals normal for that participant's height. As step length approximates normal, participants will be encouraged to walk faster and will be timed for feedback. Participants will also vary the direction of walking to include sideways and backwards, while maintaining vertical trunk alignment. Workload will be increased by introducing stairs and slopes and automaticity will be promoted by the introduction of conversation while walking around an outdoor circuit of curbs, slopes, stairs and rough terrain.

### Measurement

Since the main aim the study is to improve community ambulation, the primary outcome will be walking capacity measured as the distance covered during the 6-minunte walk test at 12 months. Given the hypothesis that improving walking capacity will directly lead to improvements in health and community participation, the secondary outcomes measures will include measures of health and community participation as well as a measure of walking quality.

Therefore, the outcome measures will be:

• Walking

Walking capacity will be assessed using the 6-minute Walk Test (distance covered in 6 min). Walking quality will be assessed using the 10-metre Walk Test (speed, stride length, cadence).

• Health

Health will be assessed by recording number of falls, number of readmissions to hospital, number of comorbidities, number of visits to the doctor, and quality of life (Euroqol EQ-5D score).

• Community participation

Community participation will be assessed using a self-efficacy questionnaire about walking ability, based on the Falls Efficacy Scale [19] and the Adelaide Activities Profile [20].

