## Methods/Design

A prospective, randomised controlled trial will be carried out (Figure 2). It will include concealed randomisation, blinded assessment and intention-to-treat analysis. 210 participants will be recruited and randomly allocated into either Group A (walking training 3 times per week for 4 months), Group B (walking training 3 times per week for 2 months) or Group C (no active intervention). Outcome measures will be collected at baseline, 2 months, 4 months, 6 months and 12 months. Both data collection and data analysis will be completed by a researcher who is blinded to group allocation. The study has obtained ethical approval from the appropriate Human Research Ethics Committees.

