### Statistical analysis

The variables that reflect walking capacity, community participation and quality of life will be analysed by pairwise comparisons between the three groups using the Students' t-test, or Wilcoxon's rank-sum test if it is clearly not normally distributed.

The other health variables: number of falls, number of readmissions to hospital, comorbidities, and number of visits to the doctors will be expressed as a proportion of events per person and analysed by pairwise comparisons between the three groups using the Chi square test.

To ascertain the threshold of post-intervention walking speed that results in the maintenance of 80% of predicted 6-min distance at 12 months, receiver operating characteristic (ROC) curves will be constructed. Youden's Index will be used to determine the cut-off point for walking speed at the end of the programs that gives the best combination of specificity and sensitivity.

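### One of the five secondary health measures, the comorbidity count, is not limited to conditions arising after randomisation, yet is analysed as events per person

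*Protocol article*

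**What the plan says.** The Measurement section of the protocol article sets out the health outcomes: "Health will be assessed by recording number of falls, number of readmissions to hospital, number of comorbidities, number of visits to the doctor", and, as a fifth item, "quality of life (Euroqol EQ-5D score" with the bracket closing there. These are secondary outcomes. The rationale given is "Given the hypothesis that improving walking capacity will directly lead to improvements in health and community participation".

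The Statistical analysis section handles EQ-5D with the walking and participation measures. It puts the other four health items, comorbidities among them, together; they "will be expressed as a proportion of events per person and analysed by pairwise comparisons between the three groups using the Chi square test". It states no change score, baseline adjustment or restriction to new conditions for any of them.

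Three other statements bear on the point:

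- Methods/Design: "Outcome measures will be collected at baseline, 2 months, 4 months, 6 months and 12 months".
- Participants: people qualify if they "are within 5 years of their first stroke".
- Randomisation: each cohort is "ranked in descending order according to comfortable walking speed over 10 m" and split into triplets. Walking speed is therefore the only matching factor, and comorbidity is not one.

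**The concern.** Falls, readmissions and doctor visits happen at a point in time and can be counted over follow-up. A comorbidity is a condition that a person carries. In people up to five years after a stroke, many such conditions will already be present at entry. The article names the item as a plain count of comorbidities and then analyses it as though each one were an event. Followed literally, a diagnosis made years before randomisation enters the 12-month comparison with the same weight as one made during the trial.

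Prior conditions are expected to be equal across randomised groups. They therefore contribute nothing on average to the between-group difference, but they do contribute variance. If training reduces new conditions, that signal has to be found against the spread of pre-existing disease. Health is part of the first main objective, and the Measurement section expects it to respond to better walking. A null result on this item could thus reflect how it was counted and say little about training.

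**Working it through.** **The plan's own figure.** The only calculation in the article is the sample size for 6-minute distance (difference 50 m, SD 100 m, two-sided 0.05, power 80%):

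- n per group = 2 × (1.960 + 0.842)² × 100² / 50² = 62.8, so 63.
- 3 × 63 = 189, and 189 / 0.90 = 210.

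This reproduces the stated 63, 189 and 210. It does not bear on the comorbidity item, but it supplies n = 63 per group for what follows.

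**Assumptions.** The article gives no comorbidity mean, SD or incidence, so these are assumed:

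- Prior conditions per person: mean 2 (SD 1.2), 3 (SD 1.5) or 4 (SD 2.0).
- New conditions over 12 months: Poisson, mean r = 0.2, 0.3 or 0.5 in controls and r/2 with training.
- New conditions are independent of prior ones, and no condition resolves.

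**Share of the count that is prior (controls).** This runs from 2 / (2 + 0.5) = 80% to 4 / (4 + 0.2) = 95%.

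**Standard errors.** The expected difference is r/2 on either count. With S = r + r/2:

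- SE on the total count = √[(2·SD² + S) / 63]
- SE on new conditions = √[S / 63]
- Power ≈ Φ(d/SE − 1.96) + Φ(−d/SE − 1.96), with d = r/2

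| Prior SD | r, control / trained | SE, total | SE, new | Ratio | Power, total | Power, new |
|---|---|---|---|---|---|---|
| 1.2 | 0.5 / 0.25 | √(3.63/63) = 0.240 | √(0.75/63) = 0.109 | 2.20 | 18% | 63% |
| 1.5 | 0.3 / 0.15 | √(4.95/63) = 0.280 | √(0.45/63) = 0.085 | 3.32 | 8% | 43% |
| 2.0 | 0.2 / 0.10 | √(8.30/63) = 0.363 | √(0.30/63) = 0.069 | 5.26 | 6% | 30% |

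The first and last rows are the extremes of the nine combinations. Simulation of 6,000 trials per scenario with a two-sample t-test gave 5.5% to 17.1% on the total count and 29.4% to 63.9% on new conditions. Taking both methods together gives roughly 6% to 18% against 30% to 64%.

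**Wider assumptions.** A second calculation used Poisson prior counts with mean 1 to 5, 0.1 to 0.5 new conditions, and a reduction of 30% or 50%. It gave 3% to 22% on the total count and 8% to 63% on new conditions. Values below 5% arise because only rejections in the correct direction were counted. The total count was less sensitive in every scenario.

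One example has 3 prior conditions, 0.3 new and a 50% reduction. The sample size per group for 80% power is then:

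- Total count: (3.3 + 3.15) × 7.849 / 0.15² ≈ 2,250 (2,251 after rounding up)
- New conditions only: (0.3 + 0.15) × 7.849 / 0.15² ≈ 157

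**Using the baseline count.** If no condition resolves, follow-up count minus baseline count equals the number of new conditions exactly. Under these assumptions, a change from baseline therefore recovers all of the lost precision.

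**The case against.** The strongest reply is that the article never says the count is a total. Grouping comorbidities with three kinds of event may mean that new conditions were intended. That reading is possible, and the text is ambiguous. But nothing elsewhere in the article restricts the count. The same measures are also taken at baseline, where a comorbidity count can only describe conditions already present. That is suggestive and not decisive, since falls at baseline would be retrospective too. If new conditions were meant, the word is still needed, because two analysts could derive different outcomes from this text.

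A second reply is that a condensed article leaves such definitions to the full protocol or analysis plan. That would hold if the article were silent. Here it names both the quantity and its analysis, and the two do not fit.

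Third, the power figures rest wholly on assumed rates and describe a comparison of means, whereas the article plans a chi-square test. This stands: they show the direction and rough scale of the loss, not the power of the planned test.

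A reader might also infer that a chance imbalance in prior disease would bias the result. It would not. Under randomisation such imbalance is ordinary sampling error covered by the 5% level, so the cost is precision. Nor does the article support a claim that training can never reverse a diagnosis. A baseline-adjusted count leaves room for conditions that resolve.

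**Conclusion.** The point holds for one secondary item. As written, the comorbidity count does not exclude conditions that predate randomisation, it is handled as events per person, and no use of the baseline value is stated. Taken literally, this inflates the standard error 2.2 to 5.3 times relative to new conditions and cuts power from roughly 30% to 64% down to roughly 6% to 18%. Those sizes depend on the assumed rates. The direction was the same in every scenario tried.

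A reader might go further and conclude that the trial cannot detect an effect on health. The article does not support that. Comorbidity is one of five health measures, and this argument does not touch falls, readmissions, doctor visits or EQ-5D. The primary outcome and the sample size are also unaffected. This is a worthwhile correction to a secondary outcome and does not threaten the main conclusions.

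**What to change.** In both the Measurement and the Statistical analysis sections, do one of the following:

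1. Define the item as comorbidities newly diagnosed since randomisation, identified by comparing each follow-up visit with the baseline record.
2. Keep the count, but compare follow-up counts between groups adjusted for the baseline count. This also allows for conditions that resolve.

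In either case, report the baseline count as a descriptor of the groups and not as an outcome.

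The cost is small: a change of wording, with no extra visits or participants, because outcome measures are already due at baseline. The first option needs named conditions kept at baseline, not just a number, and the article does not say whether they are. The second needs only the number. Neither makes the item precise. New diagnoses will be few, and even under the assumptions above power on new conditions stays below 80%, so the result should be reported as an estimate with its confidence interval.

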### Sample size

210 participants will be recruited. The sample size has been calculated to reliably detect a treatment effect size of a 50 m difference in walking capacity with 80% power at a two-tailed significance level of 0.05 on any pairwise comparison. This effect size has been derived from the walking capacity of a population of community-dwelling stroke patients who took part in the previous treadmill walking program [17]. On entry to this randomised controlled trial, the distance walked in 6 minutes was 280 (SD, 100) m using the same measurement procedure to the present proposal. The smallest number of participants to detect a 50 m difference between two groups estimated from independent samples is 63 participants per group, i.e., 189 participants in total. On the assumption that about 10% of the participants may drop out during the course of the study, we have set a target of 210 participants in total.

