**Figure 1 F1:**
[figure not shown]
**Improvements of 80 m in 6-min distance following a one-month treadmill and overground walking program (solid = experimental, dotted = control) with subsequent relapse over three months (from Ada et al **[17] with permission).

In summary, the main objectives of the AMBULATE trial are to determine (i) whether a 4-month treadmill and overground walking program is more effective than a 2-month program, compared to control, in improving walking capacity, health and community participation and (ii) the "threshold" walking speed that results in sufficient walking capacity that makes walking self-sustaining.

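### The primary outcome has three co-equal pairwise tests, each at two-sided 0.05, with no family-wise control stated: about 12% chance of at least one false positive if all groups are equal

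*Protocol article*

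**What the plan says.** The Measurement section names one primary outcome at one time point: 6-minute walk distance at 12 months. The walking-capacity variables "will be analysed by pairwise comparisons between the three groups using the Students' t-test", with the rank-sum test as the fallback for clearly non-normal data (Statistical analysis). With Groups A (4 months), B (2 months) and C (control), the pairs are A–B, A–C and B–C.

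The Sample size section aims to "reliably detect a treatment effect size of a 50 m difference in walking capacity" and does so "with 80% power at a two-tailed significance level of 0.05 on any pairwise comparison". The first objective, at the end of the Background, is "whether a 4-month treadmill and overground walking program is more effective than a 2-month program, compared to control". That wording takes in all three pairs and singles out none. The article states no primary contrast, test order, global test or adjusted level.

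**The concern.** A and B are two durations of one programme. They share a control group and are judged on the same outcome under one linked objective. Any of the three pairs could carry the trial's main conclusion, and each has a full 0.05 to spend. The error rate of the primary analysis as a whole is therefore larger than the error rate of any one test.

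The sample size is built on the same unadjusted level and leaves no room for a later split of alpha. The choice is best settled before outcome data are seen.

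**Working it through.** **Inputs (protocol article).**
- Difference 50 m; two-sided 0.05 and 80% power per pair (Sample size).
- SD 100 m, from "the distance walked in 6 minutes was 280 (SD, 100) m".
- Size before dropout: "63 participants per group, i.e., 189 participants in total"; about 10% dropout; target 210.
- Equal allocation: "The participants in each triplet will then be assigned to Group A or B or C by random allocation" (Randomisation).

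**1. The plan's own figure.** n per group = 2(z₀.₉₇₅ + z₀.₈₀)² × SD² / difference² = 2 × (1.960 + 0.842)² × 100² / 50² = 62.8, so 63. Then 3 × 63 = 189 and 189 / 0.90 = 210. All three figures reproduce at an unadjusted 0.05. With the t distribution, power at 63 per group is 79.5%.

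**2. Family-wise error with all groups equal.** The three contrasts are correlated, so 1 − 0.95³ = 14.3% and 3 × 0.05 = 15% are only upper reference values. With a pooled variance the exact value is P(Q > √2 × t₀.₉₇₅) for the studentized range Q with 3 groups and 186 df, which is 12.2%. Simulation of three separate two-sample t-tests (63 per group, 400,000 trials) gives 12.1–12.2%. Counting only A–C and B–C, it is 9.0%.

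**3. With a gate.** If the pairs are tested only after a 2-df F-test is significant at 0.05, the simulated chance of any false positive is 5.0%. The reason is structural. With three groups, if any two of the pairwise null hypotheses hold, all three do. The only intersection that needs its own test is therefore the global null, and each pair can keep the full 0.05 after the gate.

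**4. What the gate costs.** Simulated power for A–C at a 50 m difference, 63 per group. Baseline adjustment is represented by a residual SD of 100 × √(1 − r²), where r is the correlation between baseline and 12-month distance. The article does not give r, so a range is shown.

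| Analysis | Residual SD (m) | No gate | Gate, B midway | Gate, B equal to A or C |
|---|---|---|---|---|
| Plain t-tests | 100 | 79.5% | 69% | 75% |
| Adjusted, r = 0.4 | 91.7 | 86% | 77% | 83% |
| Adjusted, r = 0.5 | 86.6 | 89.5% | 82% | 87% |
| Adjusted, r = 0.7 | 71.4 | 97.4% | 94.5% | 97% |

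**5. Bonferroni for comparison.** At 0.05 / 3 = 0.0167 per pair, 2 × (2.394 + 0.842)² × 4 = 83.8, so 84 per group, 252 in total, and 252 / 0.90 = 280 with dropout. With 63 per group, power per pair is about 66%.

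**The case against.** The strongest reply is that the article is open about what it does. It states 0.05 per pair, and each pair keeps it. A reader might infer that the trial promises 5% overall and delivers 12%. The text does not support that, because no overall level is stated anywhere. This part of the reply stands in full.

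Three further points limit the size of the problem.
- The 12% needs all three groups to be equal. If one group truly differs from two that are equal, only one true null pair remains, and its error is 5% without any correction.
- The 12% counts both directions, including control beating a programme and 2 months beating 4. Under the same global null, a false result in a favourable direction (A over C, B over C or A over B) occurs in about 6.6% of trials, and a false finding that a programme beats control in about 4.5%. So 12% should not be read as the chance of wrongly declaring a programme effective. Against a one-sided 2.5% per test, these rates are still inflated.
- Whether related comparisons need adjustment is partly convention, and three separately named questions can be reported at a declared per-comparison level. That defence is weaker here, with two durations of one programme and a shared control. If it is intended, the article should say so.

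Finally, a statistical analysis plan that is not shown could add a gate, and nothing in the article forbids one. That is true, but the point does not rest on silence. The article itself gives the three pairs equal standing at 0.05 each and sizes the trial on that level. Under the planned t-tests, even a gate that leaves each pair at 0.05 takes A–C below the stated 80% power.

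**Conclusion.** The point holds as a cheap improvement and not as an error in a stated figure. As written, the primary analysis is three co-equal two-sided tests at 0.05 with no family-wise control. If all three groups are equal, at least one is falsely significant in about 12% of trials (about 9% for the two comparisons with control alone). These figures assume 63 analysed per group, normal data with equal variances, and no further adjustment specified elsewhere. The power figures also take the article's SD of 100 m as the SD at 12 months. The figures for the adjusted analysis depend on the assumed r.

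**What to change.** 1. In Statistical analysis, replace the plain t-tests for the primary outcome with a linear model of 12-month 6-minute distance on group and baseline 6-minute distance. Test the 2-df group effect at two-sided 0.05. Only if it is significant, test A–B, A–C and B–C from that model, each at 0.05.
2. If the rank-based fallback is used, gate the pairwise rank-sum tests with the Kruskal-Wallis test at 0.05.
3. In Sample size, state that 0.05 is the family-wise level for the primary outcome, and replace the 80% claim with the power of the gated procedure, giving the assumed r and a range.

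**Cost.** A few sentences. Baseline 6-minute distance is already collected, and the target of 210 does not change. The downside is power. The gate takes 5 to 11 points from A–C if the t-tests stay unadjusted, which falls below the stated 80%. Gate and baseline adjustment should therefore be adopted together: gated power is then about 77–83% at r = 0.4 and at least about 82% from r = 0.5 upwards. Naming one primary contrast or a fixed test order would also resolve the point.
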